# Metformin as adjunctive therapy in combination with multidrug treatment for multibacillary leprosy: A protocol for a randomized double-blind, controlled Phase 2 trial in Indonesia (MetLep Trial)

**DOI:** 10.12688/wellcomeopenres.19455.2

**Published:** 2024-05-09

**Keywords:** leprosy, Morbus Hansen, multibacillary leprosy, leprosy reactions, type 1 reaction, reversal reaction, type 2 reaction, erythema nodosum leprosum, host directed therapy, repurposing drugs, metformin

## Abstract

**Background:**

The clinical management of leprosy is complicated by leprosy reactions (LR) causing irreversible nerve damage and disabilities. LR often require long-term use of corticosteroids causing serious side effects. Adjunct host-directed therapy (HDT) is a potentially attractive strategy in leprosy to prevent LR and associated immunopathology, modulate immunological memory that protects against recurrence, and thereby reduce nerve damage, disability and corticosteroid-associated morbidities. Metformin, a well-tolerated, safe and cheap anti-hyperglycaemic drug, is repurposed as HDT in auto-immune and infectious diseases, like tuberculosis (TB). Metformin use in people with diabetes is associated with reduced risks of TB-infection, progression to active TB, treatment failure and TB-mortality. Given the similarities both mycobacteria share, we hypothesize that among persons with multibacillary (MB) leprosy, adjunctive metformin may prevent/mitigate LR.

**Methods:**

We will perform a double-blind controlled proof-of-concept trial in which people with newly diagnosed multibacillary leprosy will be randomized (1:1) to metformin hydrochloride 1000mg extended release once daily versus placebo for 24 weeks in addition to standard-of-care WHO MB multidrug therapy (MDT) during 48 weeks. We aim to enrol 166 participants aged between 18 and 65 years, across five clinical sites in two leprosy endemic areas in Indonesia. Primary outcomes are the proportion of participants experiencing a LR and the frequency of (serious) adverse events. Secondary outcomes are the severity and time to first LR, the cumulative corticosteroid usage, and quality of life. The total study follow-up is 48 weeks.

**Discussion:**

LR signify the most important cause of irreversible nerve damage leading to anatomical deformities and disabilities, imposing a social and financial burden on those affected. Our study aims to evaluate the efficacy, tolerability and safety of adjunct metformin added to MDT in persons with multibacillary leprosy, and explore its effects on clinical and immunological outcomes.

**ClinicalTrials.gov registration:**

NCT05243654 (17/02/2022)

## Introduction

### Background

Leprosy continues to be a public health problem worldwide, with more than 200,000 new cases recorded annually
^
1
^, predominantly affecting underserved and marginalized populations. Indonesia, a densely populated country in Southeast Asia, has the third highest number of leprosy cases in the world, after India and Brazil
^
1
^, and has pockets of high endemicity spread throughout the archipelago. In 2019, 17,439 new leprosy cases were reported in Indonesia, of which 86% were multibacillary (MB). Ten of the 34 provinces had a case detection rate of ≥1 per 10,000 population, classifying them as high disease burden areas. 6.4% of new cases had a grade 2 disability at diagnosis, indicative of diagnostic delays, and 11% were children aged 1–14 years, evidence of ongoing transmission in communities
^
1,
2
^.

### Leprosy reactions

The clinical management of leprosy is complicated by immune-mediated reactions, i.e. unpredictable episodes of exacerbated inflammation occurring before, during or after multi-drug therapy, affecting around 30–50% of people with MB leprosy
^
3
^. The majority of reactions occur during the first six months after treatment has been initiated
^
4–
7
^. Leprosy reactions (LR) are the most important cause of irreversible nerve damage leading to anatomical deformities and disabilities, imposing a physical, social and financial burden on people affected by leprosy and their households
^
8–
10
^. Two distinct LR exist: Type 1 (T1R) or reversal reactions, a delayed hypersensitivity reaction mostly occurring in the borderline forms of leprosy; and Type 2 (T2R), known as erythema nodosum leprosum, which is believed to result from immune-complex deposition and occurs in borderline lepromatous and lepromatous leprosy
^
11
^. T1R is characterised by acute inflammation and swelling of pre-existing skin lesions, oedema of extremities and face, neuritis, and infrequently systemic symptoms
^
12
^. T2R is a multisystem disease characterized by the sudden onset of painful, erythematous, subcutaneous skin lesions symmetrically distributed on face and extremities, are not related to the existing leprosy lesions and are usually accompanied by fever, neuritis, arthritis, orchitis, iridocyclitis and nephritis
^
13,
14
^.

The immunopathogenesis of LR remains poorly understood. The bactericidal effect of MDT creates a reservoir of bacterial breakdown products, which are recognized by the innate immune response and cause migration of pro-inflammatory cytokines and CD4+ T-cells to the site of infection. Activated CD8+ T-cells destroy the
*M. leprae*-infected Schwann cells leading to nerve damage. Although the clinical presentation of T1R and T2R are distinct, it is suggested that both reactions share aspects of their immunopathogenesis including enhanced Th1 responses to
*M. leprae* and macrophage activation reflected by increased levels of similar pro-inflammatory cytokines, such as IFN-γ and TNF-α,IL-1β and IL-6
^
11
^. In T1R, immunological markers like IP-10 and acute phase proteins such as CRP are substantially elevated during the reaction
^
11,
15
^. In T2R T-cell dysregulation with increased CD4+/CD8+ ratio and reduced numbers of Tregs play a key role, tipping the balance towards pro-inflammation
^
16–
18
^.

LR are a major clinical challenge as they are often chronic, recurrent and require long-term use of potent immunosuppressant’s. Oral corticosteroids remain the first-line therapy of LR although 40% of people with T1R show no clinical improvement
^
5,
19
^. Prolonged high dose corticosteroids are often necessary, causing serious adverse effects (SAE, i.e. peptic ulcer, diabetes mellitus, osteoporosis) and even death
^
20,
21
^. There is a great need to improve treatment strategies and design efficacious, safe and affordable interventions to prevent or limit the development of LR and subsequent neurological impairments and to further elucidate its immunopathogenesis.

### Adjunct Host-Directed Therapy

A new paradigm in management of infectious diseases has emerged that involves therapeutic augmentation of host immune responses and improvement of pathogen eradication, when combined with antimicrobial therapy, and in doing so tilt the host-pathogen equilibrium towards resolution
^
22,
23
^. In MB leprosy, adjunct host-directed therapy (HDT) could potentially augment antimicrobial efficacy of MDT, prevent LR and associated immunopathology, modulate immunological memory that protects against recurrence of LR, and thereby reduce nerve damage, disability and corticosteroid-associated morbidities. Repurposing drugs, such as metformin, as adjunctive HDT offer a potentially attractive approach that has a biological basis, is safe, affordable and, if effective, could be widely and relatively easily implemented.

### Metformin as a candidate for Host-Directed Therapy

Metformin is a widely used, well-tolerated, cheap oral anti-diabetic drug and is receiving renewed interest for repurposed use as HDT in auto-immune and infectious diseases, like systemic lupus erythematosus (SLE), rheumatoid arthritis and tuberculosis
^
22,
24–
29
^. Metformin has been associated with reduced cardiovascular events and all-cause mortality, independent of its glycaemic effects, with anti-inflammatory, immunomodulatory, antimicrobial, anti-cancerous, and vasculo-protective effects
^
28,
30
^. Laboratory studies showed antimicrobial effects of metformin on numerous pathogens, including
*Mycobacterium tuberculosis* (
*Mtb*)
^
22,
26,
31
^, HIV
^
32,
33
^, hepatitis C
^
34
^, dengue
^
35,
36
^ and coronavirus disease 2019 (COVID-19)
^
24,
37
^. In retrospective cohorts, metformin use in people with diabetes was associated with reduced risks of
*Mtb*-infection, progression to active TB, TB treatment failure, recurrent TB, and mortality, even after adjustment for glycaemic control and other anti-diabetic drugs
^
38–
42
^. In a randomized trial including adults with pulmonary TB, adjunctive metformin diminished excess inflammation reducing lung tissue damage and plasma inflammatory markers
^
43
^. In
*Mtb*-infected mice, use of metformin ameliorated lung pathology, reduced chronic inflammation, and enhanced the specific immune response and
*Mtb-*clearance in lungs and spleen by conventional TB-drugs
^
22
^.

At the cellular level, metformin has been proposed to enhance host immune response and reduce chronic inflammation through various mechanisms: (i) mice studies demonstrated that metformin reduced intracellular growth of
*Mtb* by inducing mitochondrial reactive oxygen species (mROS) production and phagocytosis, through metformin-induced activation of AMPK (adenosine monophosphate–activated protein kinase) and decreased mammalian target of rapamycin (mTOR) signalling
^
22,
44
^; (ii) Additionally, metformin-induced activation of AMPK stimulates differentiation of T-cells into both regulatory and CD8+ memory T-cells, shifting the balance away from pro-inflammation
^
45–
48
^. A recent study showed that metabolic reprogramming by metformin empowers CD8+ T-cells and increases the metabolic-fitness to contain
*Mtb*-infection
^
49
^; (iii) Metformin administration in humans and mice also led to major changes in the composition of the gut microbiota, suggesting a possible protective role against inflammatory conditions
^
50
^.

### Study hypotheses

Based on the phylogenetic and biological resemblance between
*Mtb* and
*M. leprae* and data from mouse and human studies pointing towards important immunomodulating effects of metformin in
*Mtb-*infection, several chronic autoimmune diseases and on metformin’s outstanding safety record, we hypothesize that metformin could be a promising candidate for adjunct HDT in combination with standard MDT for MB leprosy. Metformin could prevent LR, accelerate bacterial clearance and consequently reduce the cumulative dosage of corticosteroids and its accompanied morbidity. Metformin is expected to mitigate nerve damage and disabilities in a predominantly young and working-age population which could improve their quality of life, reduce stigmatization, discrimination and overall health care consumption and costs.

### Study aims

Although the combined available data support the safety and tolerability of concurrent antimicrobial therapy plus metformin, there is a need for a Phase 2, proof-of-concept trial with metformin combined with MDT in MB leprosy to determine its (i) tolerability and safety and (ii) efficacy based on a combination of clinical, immunological and molecular outcomes. This is deemed justified as no suitable animal models for MB leprosy are available to study the drug efficacy against LR.

In parallel, it is important to better characterize the immune and genetic host factors that drive LR in order to design host-directed preventive strategies as well as accurate diagnostic tests to reliably detect or predict the occurrence of LR. As part of the current proposal, we aim to archive prospectively collected blood samples and skin biopsies enabling future in-depth mechanistic studies adopting a system biology approach to elucidate the underlying immunopathology, metformin’s mechanism of action and evaluate novel diagnostics.

This protocol is reported in line with Standard Protocol Items: Recommendations for Interventional Trials (SPIRIT) guidelines
^
51
^.

## Protocol

### Design and setting

A double-blind, placebo-controlled randomized (1:1) Phase 2 trial evaluating the efficacy, safety and tolerability of adjunct metformin versus placebo for 24 weeks, in addition to standard-of-care MDT (rifampicin 600mg and clofazimine 300mg once a month supervised, 50mg of clofazimine and 100mg of dapsone daily unsupervised) in the management of individuals with newly diagnosed MB leprosy (
Figure 1). The study will take place in five primary health centers (puskesmas) in Jayapura, Papua, and Gowa, Sulawesi, which are areas of high endemicity of leprosy in Indonesia, most of which are MB leprosy. This is protocol version 5.0, dated January 30
^th^ 2024.

**Figure 1. f1:**
[figure not shown]
Schematic of study design.

### Outcomes

**
*Primary efficacy outcome*
**

The proportion of participants experiencing a LR during study follow-up (total 48 weeks).

**
*Primary safety outcome*
**

The proportion of participants with at least one adverse event (AE) within the first 24 weeks of the study.

**
*Secondary outcomes*
**

1.   The proportion of participants experiencing a T1R or T2R (as separate outcomes) at 24 and 48 weeks.

2.   Time to first LR and time to first T1R and T2R as separate outcomes, over the full 48 weeks.

3.   Severity of T1R and T2R at onset based on investigator-assessed validated Clinical Severity Scores
^
52,
53
^.

4.   The proportion of participants with at least one SAE within the first 24 weeks of the trial.

5.   The total number of AE within the first 24 weeks of the trial.

6.   Cumulative corticosteroid usage in participants with a leprosy reaction.

7.   The proportion of participants experiencing clinical nerve function impairment (NFI) developed over the full 48 weeks.

8.   Quality of Life (QoL) at enrolment, half-way treatment intervention (12 weeks), end of treatment intervention (24 weeks), and end of study (48 weeks) using validated local language versions of the Dermatology Life Quality Index (DLQI) and the 36-item Short Form Survey (SF-36).

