### Inclusion/exclusion criteria

Participants will be considered eligible for enrolment in this trial if they fulfil all the inclusion criteria and none of the exclusion criteria. The trial will enrol participants aged between 18–65 years presenting with newly diagnosed MB leprosy and who have no LR and/or NFI with indication for corticosteroids at the time of diagnosis or trial enrolment. Screened participants who are not eligible will be recorded in a screening log with reasons for screening failure, and will receive local standard-of-care.

**
*Inclusion criteria*
**

Participant aged ≥18 and ≤65 years.Participant is newly diagnosed with MB leprosy and receiving MDT ≤28 days.Participant is willing and able to give informed consent for participation in the trial.Participant is willing to adhere to study follow-up schedule for 48 weeks.

**
*Exclusion criteria*
**

Participant has received MDT >28 days for the current episode of MB leprosy, prior to study enrolment.Presence of leprosy reaction or nerve function impairment requiring systemic corticosteroids on screening or enrolment evaluation.Participants who have been treated for leprosy in the past.Chronic systemic corticosteroid use for any other medical condition on screening evaluation (chronic use defined as ≥ 2 weeks).History of diabetes mellitus or diabetes mellitus diagnosed on screening evaluation (random blood glucose is elevated ≥200 mg/dL (or ≥11,1 mmol/L) or fasting blood glucose ≥ 126 mg/dL (or ≥7.0 mmol/L)).History of hypoglycaemia (random blood glucose <55 mg/dL (or <3.0 mmol/L)).History of cardiac failure, ischaemic heart disease, alcoholism, history of lactic acidosis or states associated with lactic acidosis such as shock or pulmonary insufficiency, and conditions associated with hypoxia.History of intolerance or hypersensitivity to metformin.Estimated glomerular filtration rate (eGFR) ≤30 mL/min/1.73m
^2^, calculated by the CKDEPI equation, on screening evaluation
^
61,
62
^.ALT/SGPT ≥3 times the upper limit of normal (ULN) on screening evaluation.HIV-positive on screening evaluation (screening applicable for sites in Papua only
^
a

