For all secondary outcomes, we make a comparison correcting for BI and study site, except for those related to (S)AE (i.e. outcome 4 and 5). Outcomes 1, 4 and 7 are analyzed in the same way as the two primary outcomes. For time to first LR, we compute and plot Kaplan-Meier curves by treatment arm and fit Cox proportional hazards models that include BI and study site. Although the value of the hazard ratio cannot be given a causal interpretation, we include this model because it is the standard approach in time-to-event analyses. However, we will also perform an analysis using restricted mean survival time as outcome. Severity of T1R and T2R at onset will be compared with a regression model that is determined based on the distribution of the scores. The total number of AEs within the intervention period will be compared via a quasi-Poisson regression model. Cumulative corticosteroid usage is modelled via linear regression. For the participants that are still using corticosteroids at 48 weeks, values will be treated as right censored. If needed, we will use the Box-Cox procedure to determine an appropriate transformation. We will allow for extra values at zero via a zero-inflated model, in case some of the participants with a mild reaction do not receive corticosteroids. Quality of life is compared over the four time points using mixed effects models. If the distribution in QoL is too skewed, we will use beta regression using generalized estimating equations to correct for correlation within individuals.

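### Cumulative corticosteroid use (secondary outcome 6) is compared only among participants who develop a leprosy reaction, so it is not a randomised comparison and leaves out the steroid saved by prevention

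*Protocol article*

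**What the plan says.** The Outcomes section defines secondary outcome 6 as "Cumulative corticosteroid usage in participants with a leprosy reaction". The section on analysis of the secondary outcomes confirms that population. It plans a linear regression of cumulative use and allows for "extra values at zero via a zero-inflated model, in case some of the participants with a mild reaction do not receive corticosteroids". Zeros are thus foreseen only for reactors with a mild reaction, and participants without a reaction do not enter with a zero. Adjustment is general: "For all secondary outcomes, we make a comparison correcting for BI and study site", apart from the adverse-event outcomes.

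The Study hypotheses section expects metformin to prevent LR and "consequently reduce the cumulative dosage of corticosteroids and its accompanied morbidity". The Abstract lists cumulative corticosteroid usage without any restriction to reactors.

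Secondary outcome 3 is "Severity of T1R and T2R at onset based on investigator-assessed validated Clinical Severity Scores", and the analysis text says "Severity of T1R and T2R at onset will be compared with a regression model that is determined based on the distribution of the scores". Neither sentence names a population, but a score at onset exists only where there is an onset.

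The exclusion criteria include "Presence of leprosy reaction or nerve function impairment requiring systemic corticosteroids on screening or enrolment evaluation", so the protocol recognises NFI as a reason for systemic steroids alongside LR.

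**The concern.** LR over 48 weeks is the primary efficacy outcome and the event metformin is meant to prevent. Outcome 6 selects on that event. If metformin works, the metformin reactors are those who reacted despite treatment, while the placebo reactors include people whose reaction metformin would have prevented. The two groups can then differ in anything that determines who reacts. BI and site are only two such factors, so adjusting for them does not restore comparability.

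The restriction also removes the benefit that the hypothesis describes. A participant who needs no steroid because no LR occurred is a success of treatment, yet contributes nothing. Steroid given for NFI without an LR, for example in silent neuropathy, is not counted either.

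Less steroid exposure is a central part of the rationale, and the Discussion says positive results will inform a Phase 3 trial. A steroid result that cannot show prevention could mislead that step. The protocol warns that the hazard ratio has no causal interpretation but gives no such warning here.

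**Working it through.** **Inputs from the protocol (Sample size):** 75 per arm, control LR 50%, relative risk reduction 50% (so 25% on metformin), two-sided 0.05, stated power 89%. The protocol gives no steroid doses, no mild/severe mix and no power for outcomes 3 or 6. Those inputs below are assumptions.

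**1. The plan's own figure.** With a pooled-variance test, the average proportion is 0.375.
- Null SE = √(2 × 0.375 × 0.625 / 75) = 0.0791.
- Alternative SE = √((0.25 + 0.1875) / 75) = 0.0764.
- Power = Φ((0.25 − 1.96 × 0.0791) / 0.0764) = 89.3%. The stated 89% reproduces.

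**2. Participants contributing.** 75 × 0.50 + 75 × 0.25 = 37.5 + 18.75, about 56 of 150, with twice as many from placebo as from metformin.

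**3. What restriction removes.** If participants without an LR receive no steroid, mean use per randomised participant = P(LR) × mean use among reactors. Hence

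all-randomised ratio = LR risk ratio × ratio among reactors = 0.50 × ratio among reactors.

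If prevention is unrelated to severity, the ratio among reactors is 1.00 and the all-randomised ratio is 0.50. The planned comparison shows no difference where mean use has halved.

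**4. Range when prevention depends on severity.** Let a share m of control reactions be mild, with mild dose r times the severe dose. Mean dose among control reactors is m·r + (1 − m). Metformin prevents half of all reactions. The grid is m = 0.3, 0.5, 0.7 and r = 0, 0.25, 0.5.

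| Reactions prevented | Ratio among reactors | Ratio in all randomised |
|---|---|---|
| Mildest first | 1.18 to 2.00 | 0.59 to 1.00 |
| Unrelated to severity | 1.00 | 0.50 |
| Most severe first | 0.00 to 0.82 | 0.00 to 0.41 |

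One cell in full, m = 0.5 and r = 0.25: control mean = 0.5 × 0.25 + 0.5 = 0.625. Mildest first leaves only severe reactions: 1 / 0.625 = 1.60, and 0.80 in all randomised. Most severe first leaves only mild ones: 0.25 / 0.625 = 0.40, and 0.20 in all randomised. The all-randomised 1.00 arises where mild reactions get no steroid at all, so preventing them saves none.

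**5. A less extreme split.** Take m = 0.5 and r = 0.375, so the control mean is 0.6875.
- 75% of mild and 25% of severe reactions prevented: metformin mean = 0.25 × 0.375 + 0.75 = 0.844. Ratio among reactors 1.23 (+23%), all randomised 0.61 (−39%).
- Split swapped: 0.75 × 0.375 + 0.25 = 0.531. Ratio among reactors 0.77 (−23%), all randomised 0.39 (−61%).

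**6. Continuous severity (relevant to outcome 3 too).** Assume a standard normal latent severity, with an LR in controls above 0. Mean severity among control reactors is 0.80.
- Metformin removes only the weaker reactions (threshold 0.674): reactor mean 1.27, ratio 1.59, all randomised 0.80. In 4,000 simulated trials with 75 per arm, the reactor comparison favoured placebo in over 99% and was significant in 88%.
- Metformin also makes every reaction milder by 0.674: reactor mean 0.60, ratio 0.75, all randomised 0.37. The reactor comparison pointed the wrong way in 9%.

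**The case against.** These are two of eight secondary outcomes in a proof-of-concept trial. The primary efficacy outcome is analysed in all randomised participants, and the protocol attaches no decision rule to outcomes 3 or 6. The trial also hopes to mitigate reactions, and steroid need among reactors, read beside the LR proportion, is a fair description of that. All of this stands. It limits the weight of the point and is a reason to keep the reactor-only summary, but a description of reactors is still not an effect of randomised treatment.

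A reader might infer that an effective drug will appear to increase steroid use. The documents do not support that. Reversal requires metformin to prevent mainly milder reactions, and swapping the assumed split turns +23% into −23%. If metformin did not change who reacts, this selection bias would not arise.

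A reader might also treat outcome 3 as explicitly restricted in the same way. Its restriction is implied by what a score at onset is, not stated as an analysis exclusion.

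The NFI gap is narrower than it may look. The T1R definition includes neuritis alone, with or without NFI, so much NFI may already count as an LR, and NFI is a separate outcome in all participants. The size of what remains cannot be estimated from the protocol.

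Finally, it is tempting to say the data for an all-randomised analysis are already collected. Table 2 shows no row for concomitant medication or steroid dose, so that needs checking.

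**Conclusion.** The point holds for outcome 6. Its definition fixes a population selected on the primary outcome, so this is not a detail left to the SAP. The comparison is not between randomised groups and omits the saving the hypothesis names. At the protocol's rates about 56 of 150 participants contribute, and the ratio among reactors misses the LR risk ratio of 0.50: a true 0.50 shows as 1.00 when prevention is unrelated to severity. That result assumes non-reactors receive no steroid. The wider ranges (1.18 to 2.00, or 0.00 to 0.82) also rest on assumed severity and dose mixes, so the direction of any distortion is not known in advance. Outcome 3 carries the same selection by implication and warrants an interpretive caveat. This should be fixed, but it does not threaten the primary analysis.

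**What to change.** **Outcome 6.** Define it as cumulative corticosteroid use, in a common equivalent, from randomisation to week 48 in all randomised participants, given for LR or NFI, with zero for those observed to receive none. Analyse it with a two-part model or a robust mean difference, adjusted for BI and site. Treat loss to follow-up as censored or missing, never as zero. The planned right-censoring of participants still on steroids at week 48 must be reconciled with this definition, since their use up to week 48 is observed. Confirm that steroid doses are recorded for participants without an LR. Keep the reactor-only comparison as descriptive.

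**Outcome 3.** Label the between-arm comparison as descriptive and not a randomised effect. Alternatively, add a supportive ordinal analysis in all randomised participants with no reaction as the lowest category, done separately for T1R (scale 0 to 48) and T2R (0 to 30). A single combined rank would mix two scales. With about 94 of 150 tied at no reaction, it would also largely repeat the primary outcome.

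**Cost.** An amendment to the outcome wording, with the approvals the protocol requires while the trial is enrolling, plus analysis work. If steroid use outside an LR is not recorded, a data-capture item is also needed. The all-randomised result mixes occurrence with amount, and the descriptive reactor-only table separates the two. Neither treatment nor the visit schedule changes.
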